8.2 Number of participants
     Control group(C group): 30
     Recruitment group(R group): 30

9. Methods
10.1. Enrollment
 The patients who are undergoing elective RARP under general anesthesia and adequate for inclusion & exclusion criteria will be enrolled after informed consent. 

10.2. Informed consent
Researchers will obtain written forms of consent after sufficient explanation about the research using preorganized explanatory note.

10.3. Ramdomisation
Before registration of participants, a block assign list according to the random number table will be made, which consists of blocks sized 4 which contains 2 patients from control group(A) and 2 patients from experimental group(B) (AABB, BBAA, ABAB, BABA, ABBA, BAAB), and blocks sized 6 which contains 3 patients from each group (AAABBB, AABABB, AABBAB, AABBBA, BBBAAA, BBABAA, BBAABA, BBAAAB, ABAABB, ABABAB, ABABBA, ABBBAA, ABBAAB, ABBABA, BAAABB, BAABAB, BAABBA, BABBAA, BABABA, BABAAB). The participants will be assigned to control group and experimental group according to this random assign list. 
All the process of randomisation will be conducted by an anesthesiologist who is not involved in the study, and the assignment will be kept in a sealed envelope which is not accessible to the researchers until induction of anesthesia. 

10.4. Sample size
  The primary outcome is the incidence of perioperative pulmonary complications. Sample size calculation was based on a previous study in which the incidence of atelectasis after laparoscopic surgery was 30% [11]. We considered a reduction of the incidence by 90% to be statistically significant. Thus, we calculated that 30 patients would be needed in each group, using a two-sided test with 80% power and a 5% ¥á-error, allowing for 20% dropouts. 

10.5. Study protocol
All the clinical procedures other than RM will be conducted in same measures in both group.
- The patients who are undergoing elective RARP under general anesthesia will be enrolled.
- The participants will be randomly allocated into 2 groups.
- After induction, 5 cmH2O of PEEP will be applied to all patients without RM in the control group (group C) and after RM in the recruitment group (group R). 
-	Participants will be premedicated with 2 mg of midazolam.
- Induction and maintenance of anesthesia will be done with propofol and remifentanil using an Orchestra infusion pump system (Fresenius Vial, Brezins, France). The concentrations of propofol and remifentanil wil be adjusted with TCI to maintain a bispectral index (BIS) of 40–60 (measured with an A-2000 BISTM monitor; Aspect Medical Systems Inc., Natick, MA, USA). 
- Muscle relaxation will be done before tracheal intubation using 0.6 mg/kg of rocuro nium.
- During surgery, a tidal volume of 6–8 mL/kg of predicted body weight, PEEP of 5 cmH2O, FIO2 of 0.4, inspiratory:expiratory ratio of 1:2, PIP less than 35 cmH2O in pressure control mode will be maintained, and RR will be adjusted to maintain ETCO2 of 35~40 mmHg. 
- Lungs are going to be recruited by increasing the PEEP gradually, from 4 cmH2O (2 breaths) to 6 cmH2O (2 breaths), 8 cmH2O (2 breaths), and finally 16 cmH2O (10 breaths). After 10 breaths with 16 cmH2O, PEEP is going to be decreased stepwise as before. 
- The surgical procedure will be conducted using robotic sytem(da Vinci; Intuitive Surgicla, Inc., Sunnyvale, CA), and intraabdominal pressure of 17 mmHg will be maintained during the procedure.
- During the intraoperative and PACU periods, arterial blood gas analyses will be performed as baseline measurements before application of RM and PEEP (T1), 30 min after induction of CO2 pneumoperitoneum (T2), 90 min after induction of CO2 pneumoperitoneum (T3), and 30 min after arrival in the PACU in room air (T4). 
- The patient-tested baseline pulmonary function testing will be performed using a portable spirometer (MicroLoop¢â; Carefusion, Basingstoke, UK) on a day before operation, before leaving the post-anaesthetic care unit (PACU), and on the postoperative second day. 

- Low-dose chest computed tomography (CT) will be performed on the postoperative second day for evaluation of postoperative atelectasis. 
10.6. Monitoring parameters and laboratory tests
1) Patient demographics and monitoring parameters
Patients¡¯age, height, weight, BMI, comorbidities, past medical histories, medications, operation time, anesthesia time, estimated blood loss, amounts of crystalloid and colloid infused during surgery, transfusion, respiratory index (tidal volume, RR, ETCO2, PIP, PEEP, AaDo2, static & dynamic compliance, FIO2,), blood pressure and heart rate changes before and after RM will be documented.

2) Laboratory and clinical tests
Arterial blood gas analysis (pH, pCO2, pO2, Lactate, hematocrit, HCO3-, TCO2, base excess, saturation, hemoglobin), alveolar-arterial oxygen tension difference, pre- and postoperative pulmonary function test, chest CT scan will be conducted.

10.7. Outcome variables and analyses
1) Primary outcome – the incidence of perioperative pulmonary complications
2) Secondary outcome – differences in static & dynamic compliance of each group, changes in pulmonary function test results
3) Other variables – differences in arterial blood gas analysis results, blood pressure and heart rate changes before and after RM 

10.8. Safety assessment
 Safety assessment will be conducted for all the patients who are included in the study. If an adverse event occurs, it will be documented with whether there is any causal relationship between the event and research methods, and its severity, importance, duration will be assessed afterwards. Interventions for adverse events and their results will also be documented. Adverse events will be assessed and intervened immediately according to any abnormal test results, and additional tests other than planned ones can be done if nessessary.

1)Severity
Adverse events will be classified into 3 classes according to following definitions:
Mild adverse event is temporary and does not cause impairment in daily activies.
Moderate adverse event causes slight impairment in daily activies.
Severe adverse event causes major impairment in daily activies.

2)Cause - result relationship
Cause - result relationship will be classified into 5 classes: ¡®definitely related', 'highly likely to be related', 'likely to be related', 'not likely to be related', 'difficult to determine causalty'.

3)Category of adverse events 
Adverse events related to PEEP or RM
Pneumothorax occurs rarely due to PEEP or RM, but it is known that small amount of pneumothorax tends to be spontaneously resolved. Also, because this adverse event generally occurs in process of applying PEEP or conducting RM, there is no difference expected in the category of adverse events between R group and C group.

10.9. Statistical analysis
SPSS for Windows software (ver. 19.0; SPSS Inc., Chicago, IL, USA) will be used for statistical analyses. Patients¡¯age, height, weight, BMI, comorbidities, past medical histories, medications, operation time, anesthesia time, estimated blood loss, amounts of crystalloid and colloid infused during surgery, transfusion, respiratory index (tidal volume, RR, ETCO2, PIP, PEEP, AaDo2, static & dynamic compliance, FIO2,) arterial blood gas analysis (pH, pCO2, pO2, Lactate, hematocrit, HCO3-, TCO2, base excess, saturation, hemoglobin), alveolar-arterial oxygen tension difference, pulmonary function test results will be analysed and compared between 2 groups. 
Statistical differences in nominal data will be analysed by the chi-square test. Statistical differences in continuous data will be compared using the Kruskal–Wallis test. Post-hoc subgroup analyses will be performed with the Mann–Whitney U test. A P value < 0.05 will be considered statistically significant. 

11. Reference
5) Tokics   L,   Hedenstierna   G,   Strandberg   A,   Brismar   B, Lunquist H. Lung collapse and gas exchange during general anesthesia. effects of spontaneous breathing, muscle paralysis,  and  positive  end-expiratory pressure.  Anesthesiology 1987; 66: 157—67. 

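### Section 10.9 names one two-group rank test twice for continuous outcomes and leaves the T1 blood gas unused as a baseline

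*Protocol*

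**What the plan says.** Section 10.5 sets up a two-arm trial: "The participants will be randomly allocated into 2 groups". Section 10.4 plans that "30 patients would be needed in each group".

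Section 10.9 lists the ventilation, blood gas and spirometry variables for comparison between the two arms. It then fixes the methods: "Statistical differences in continuous data will be compared using the Kruskal–Wallis test", followed by "Post-hoc subgroup analyses will be performed with the Mann–Whitney U test". No subgroup is named there or elsewhere in the protocol.

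On baselines, section 10.5 says "arterial blood gas analyses will be performed as baseline measurements before application of RM and PEEP (T1"), with later samples at T2 and T3 during pneumoperitoneum and at T4 in the PACU on room air. Spirometry is done the day before surgery, at the end of the PACU stay, and on postoperative day 2.

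Section 10.7 gives the secondary outcomes as "differences in static & dynamic compliance of each group, changes in pulmonary function test results". Blood gases come under other variables, as differences, with no reference to T1.

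**The concern.** Kruskal-Wallis is an overall test for several groups, and a pairwise follow-up makes sense only when there are at least three. With two arms there is nothing to follow up. A reader cannot tell whether the post-hoc sentence repeats the main comparison or announces subgroup analyses that were never specified.

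The named tests also take no covariate. Blood gases have a true pre-intervention value for each patient, and the stated analysis does not use it when comparing later values. Intraoperative oxygenation is one of the objectives in section 5.6, so with 30 patients per arm the lost precision matters. For spirometry the loss is smaller, because a change already draws on the baseline.

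**Working it through.** **Inputs.** Two arms (10.5); 30 per arm (10.4); Kruskal-Wallis, then Mann-Whitney (10.9); T1 before the intervention (10.5); spirometry outcome defined as a change (10.7). The protocol gives no standard deviation, target difference or baseline-to-follow-up correlation for any continuous outcome. The correlation r is therefore assumed and shown over a range.

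**The plan's own figure.** The only stated size, 30 per arm, belongs to the binary primary outcome. It can be reproduced from 30% against 3% (a 90% reduction), two-sided 5%, 80% power, with the arcsine formula n = 2[(1.960 + 0.842)/h]², where h = 2(arcsin√0.30 − arcsin√0.03) = 0.811. This gives 24 per arm, and 24/(1 − 0.20) = 30. Nothing below changes it.

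**Step 1: are the two tests the same?** With two groups the Kruskal-Wallis statistic H equals the square of the Mann-Whitney normal deviate (without continuity correction) and is referred to chi-square on 1 degree of freedom. The p-values therefore coincide. In 4,000 simulated data sets of 2 × 30 patients (2,000 without ties, 2,000 with ties) the largest difference was below 10⁻¹².

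**Step 2: what does ignoring or differencing the baseline cost?** Take equal variance at baseline and follow-up, scaled to 1. The residual variance of the group comparison is then:
- follow-up only: 1
- change score: 2(1 − r)
- ANCOVA on baseline: 1 − r²

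| r (assumed) | Change score | ANCOVA | ANCOVA saving vs follow-up only | ANCOVA saving vs change score |
|---|---|---|---|---|
| 0.3 | 1.40 | 0.91 | 9% | 1 − 0.91/1.40 = 35% |
| 0.5 | 1.00 | 0.75 | 25% | 1 − 0.75/1.00 = 25% |
| 0.7 | 0.60 | 0.51 | 49% | 1 − 0.51/0.60 = 15% |
| 0.8 | 0.40 | 0.36 | 64% | 1 − 0.36/0.40 = 10% |

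The follow-up-only column is the comparator for blood gases, where no change from T1 is specified. The change-score column is the comparator for spirometry. These percentages do not depend on the number of patients.

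**Step 3: what this means for power.** Simulation with 3,000 runs, 30 per arm, normal data and an assumed difference of 0.6 SD:

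| r | Kruskal-Wallis, follow-up only | Kruskal-Wallis on change | ANCOVA |
|---|---|---|---|
| 0 | 59% | 36% | 62% |
| 0.3 | 61% | 47% | 67% |
| 0.5 | 60% | 60% | 74% |
| 0.7 | 60% | 82% | 89% |
| 0.8 | 60% | 94% | 97% |

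The small ANCOVA advantage at r = 0 cannot come from the baseline. It reflects the slight loss from ranking normal data. The rest of the gap grows with r.

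**The case against.** The strongest reply is that a rank test between two randomised groups at one time point is valid, and that running it twice returns the same p-value, so no error rate is inflated and no conclusion changes. Covariate adjustment and confidence intervals are often left to an analysis plan, which is not shown here. All of this stands. It limits the point to efficiency and clarity. It does not remove it, because the protocol itself fixes the tests, and the post-hoc sentence is redundant or undefined as written.

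The size of the gain is also fairly contested. No correlation is given. T1 precedes PEEP and pneumoperitoneum, and T4 is on room air, so r for blood gases could be low; at 0.3 the saving is only 9%.

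Three stronger readings are tempting, and the documents do not support them.
- *The preoperative spirometry is ignored.* Section 10.7 defines that outcome as a change, which uses it.
- *Kruskal-Wallis will be run across T1 to T4 within an arm.* That would break independence and make the test very conservative (about 0.5% rejection of a true null at a within-patient correlation of 0.5). But 10.9 describes comparison between the arms, not over time.
- *Oxygenation results are confounded by inspired oxygen.* At T4 both arms breathe room air, and no comparison pooled over the four times is planned. The FIO2 at T1 is not stated explicitly either: 0.4 is listed among the settings during surgery, together with the PEEP that T1 precedes.

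**Conclusion.** The point holds as an improvement in efficiency and wording. In a two-arm trial, Kruskal-Wallis followed by Mann-Whitney is one test named twice, or a subgroup analysis without subgroups. The T1 blood gas is collected as a baseline and then not used as one. Spirometry change scores use their baseline, but less efficiently than ANCOVA.

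For blood gases the avoidable residual variance is 9% at r = 0.3, 25% at 0.5 and 49% at 0.7. For spirometry, measured against a change score, it is 25% at 0.5 and 15% at 0.7. These figures rest on assumed correlations and equal variances; the power figures also assume normal data and a 0.6 SD difference. A reader might infer an invalid test or a wrong error rate; the planned between-arm comparison has neither problem. The affected results are secondary and other outcomes. The chi-square analysis of the primary outcome and the sample size stay as they are.

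**What to change.** In section 10.9, delete the Kruskal-Wallis sentence and the post-hoc sentence, and put in their place:

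- **Blood gas outcomes at T2 and T3:** a linear mixed model with the T1 value as covariate and terms for group, time and group-by-time.
- **Blood gas outcomes at T4:** a separate ANCOVA with T1 as covariate, since this sample is on room air.
- **Spirometry at PACU and postoperative day 2:** ANCOVA or a mixed model with the preoperative value as covariate.
- **Compliance:** adjust for baseline only if a value before the recruitment maneuver is recorded. Sections 10.5 and 10.6 give no measurement times for it, so this should be stated.
- **Variables measured once:** Mann-Whitney, named once.
- **Reporting:** group differences with 95% confidence intervals. Any log or rank version should be fixed for each outcome in advance, so that the choice does not depend on the data.

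If real subgroup analyses were intended, name the subgroups instead of leaving the sentence open.

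The cost is a change of analysis wording. The blood gas and spirometry baselines are already scheduled, so no measurement or patient is added. The downside is a mild modelling assumption about how follow-up depends on baseline, which the pre-specified transformed version largely covers.
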